### The treatment of removed cases

2.4

1.When a subject drops out, the chief physician should employ methods such as going to the subject's house, making phone calls, or sending letters to try to contact the subject to ask for the reasons for study dropout, to record the last date of treatment, and to complete the study analysis.2.The chief physician should use alternate treatment measures according to the actual situation of the subjects who are no longer in the study because of adverse reactions or treatment ineffectiveness.3.When a subject is assigned a random number, he/she becomes an object of the experimental observation, regardless of future diagnosis or the integrity of the treatment.4.After completing at least half the treatment course, a subject who drops out will be considered an effective evaluation case; less than half of the patients with adverse reactions will not be evaluated and will be evaluated only for adverse reactions. However, patients who violate the test plan (eg, violation of the combination of drugs, violation of the inclusion criteria, and medication compliance) will not be evaluated for efficacy or adverse reactions.

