**Methods/Design::**

A total of 333 participants will be randomly assigned to 2 acupoint treatment groups or 1 nonacupoint control group in a 1:1:1 ratio by a central stochastic system. The acupuncture groups are: the single acupoint group: Shenmen (HT7); and he compatibility acupoint group: Shenmen (HT7), Baihui (DU20), and Sanyinjiao (SP6). The observation period of this trial will be 10 weeks. All patients will be followed for 1 week before randomization (baseline phase). After randomization, the patients will receive 30 minutes of electro-acupuncture once per day for 5 weeks. In the fourth week after the treatment, follow-up will be performed once. The primary outcome will be the Pittsburgh sleep quality index score at 1 week before randomization and 2 and 8 weeks after randomization. The secondary outcomes will include data from sleep diaries, Athens insomnia scale scores, ShortForm-36 Health Survey scores, electroencephalogram technology results and polysomnogram) results. Patients will be required to complete a sleep diary every day during the treatment period. Patients will also undergo electroencephalogram technology and polysomnogram 1 week before randomization and 5 weeks after randomization. The other secondary outcomes will be measured 1 week before randomization and 5 and 9 weeks after randomization.

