#### 2.2.6 Management of Adverse Events

2.4.1

1.Records and reportsThe investigator should explain to the patient that they (or a family member) should accurately report all physical changes after treatment. The doctor should avoid leading questions and observe the adverse reactions when observing the effects. Whether adverse effects or adverse events are associated with the treatment methods in this study, they should be detailed in the record, including adverse reaction times, symptoms, physical signs, adverse reaction degrees, adverse reaction durations, laboratory examination indices, treatment methods, and results and follow-up times.If serious adverse events occur during the course of treatment, the investigator must report the adverse events to the clinical research department within 20 hours or no later than the second working day. The investigator will sign and date the report. The investigator should record when, how and to whom they reported the serious adverse events in the original data.2.Treatment of patientsIn cases of adverse events, the investigator may take necessary measures according to the condition of the disease until the situation is stable. Patients with abnormal test results should be tracked until the results return to normal. The investigator will decide whether to end the observation. The follow-up method can be selected according to the degree of adverse events, including hospitalization, outpatient observation, home visit, telephone call, and communication.

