#### Outcome measurement

2.7.1

The primary outcome measure in this trial will be the PSQI, and the secondary outcome measures will include the sleep diary, Athens insomnia scale score, SF-36 score, ET results, and PSG results.

PSQI^[16,17]^ is a self-rated questionnaire that assesses sleep quality and disturbances over a 1-month time period. Nineteen individual items generate 7 “component” scores: subjective sleep quality, sleep latency, sleep duration, habitual sleep efficiency, sleep disturbances, use of sleeping medication, and daytime dysfunction. The sum of scores for these 7 components yields 1 global score. All patients will complete the PSQI 1 week before randomization and in the fifth and eighth weeks after randomization.

The sleep diary^[18]^ will be used to record the patients’ sleep and to collect sleep information to assess the therapeutic effect after treatment. Patients will need to complete the sleep diary every day during the treatment period and complete the CRFs only once a week.

The Athens insomnia scale will be used to record the patients’ self-assessment of sleep disorders. The items include sleep latency, waking up at night, waking up earlier than expected, total sleep time, sleep quality, emotions during the day, physical functioning during the day and daytime sleepiness. Patients will need to complete the Athens insomnia scale 1 week before randomization and at the fifth and the ninth week after randomization.

The SF-36^[19]^ questionnaire consists of 36 items containing 8 subscales each. These subscales consist of 2 higher-level summary scales, namely, the physical (physical function, physical role function, bodily pain, and general health) and psychological (vitality, social function, emotional role function, and mental health) summary scales. Patients will complete the SF-36 1 week before randomization and at the fifth and ninth week after randomization.

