ET is a pioneering analysis technology in China that provides noninvasive, quantitative detection of the neurotransmitters involved in brain activity and brain function regardless of physiological or pathological condition. It can be applied to the study of brain function, providing objective mathematical evidence for the study of neuropsychiatric diseases and clinical treatment guidance. Patients will need to perform ET 1 week before randomization and at the third and fifth weeks after randomization. Patients will also need to undergo PSG 1 week before randomization and at the fifth week after randomization.

Biological indicators, including body temperature, heart rate, respiration and blood pressure, will be measured 1 week before randomization and at the fifth and ninth weeks after randomization. Sex, age, culture, occupation, height, weight, and acupuncture expectation will also need to be recorded.

Any adverse events and the manner in which they are addressed will be recorded during the 4 treatment weeks and the 12 follow-up weeks. These adverse events include bleeding, hematoma, fainting, serious pain, and local infection. If patients suffer any serious adverse events, all details will be documented. The patients’ blood, urine, stool, liver function, renal function, and electrocardiogram analysis results will be recorded 1 week before randomization and at the fifth week after randomization.

Drop-outs, withdrawals, and patient compliance will be recorded during the treatment weeks and the 4 follow-up weeks. All patients will be recorded until the end of the trial.

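### The protocol contradicts itself on whether patients who stop acupuncture stay under outcome assessment, so outcome-related PSQI values may go uncollected

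*Protocol article*

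**What the plan says.** Two sets of statements bear on this point.

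**Pointing towards exit from the study (section 2.4)**
- Item 1: the chief physician must reach a dropout by home visit, phone or letter "to ask for the reasons for study dropout, to record the last date of treatment, and to complete the study analysis".
- Item 2: it provides other care for "subjects who are no longer in the study because of adverse reactions or treatment ineffectiveness".
- Item 4: "After completing at least half the treatment course, a subject who drops out will be considered an effective evaluation case".

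**Pointing towards continued observation**
- Section 2.4 item 3: once given a random number, "he/she becomes an object of the experimental observation, regardless of future diagnosis or the integrity of the treatment".
- Section 2.7.1: "All patients will complete the PSQI 1 week before randomization and in the fifth and eighth weeks after randomization".
- Section 2.7.1, after the sentence on drop-outs and withdrawals: "All patients will be recorded until the end of the trial".

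Section 2.9.1 names both PP and ITT analyses of change from baseline. Section 2.4.1, on adverse events, adds: "The investigator will decide whether to end the observation". The abstract gives a different timetable for the primary outcome: "Pittsburgh sleep quality index score at 1 week before randomization and 2 and 8 weeks after randomization".

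**The concern.** The text does not separate stopping acupuncture from leaving the trial. One site could read section 2.4 items 1, 2 and 4 and close the record of a patient who gives up for lack of effect. Another could read item 3 and section 2.7.1 and continue the questionnaires. Both would be following the protocol.

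This concerns what is measured after a stop. Who is later removed from an analysis set is a separate question. It cannot be left to a statistical analysis plan, because no analysis rule recovers a PSQI that was never taken. If patients leave because treatment is not working, the missing values are plausibly worse than the observed ones, and there are likely to be more of them in the arm with the smaller effect. The ITT analysis would then rest on a selected group.

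**Working it through.** **Step 1: when a dropout becomes evaluable.** Section 2.6 gives 25 sessions over 5 weeks, five per week. Half of 25 is 12.5, so the threshold in section 2.4 item 4 is met at session 13. Week 3 holds sessions 11 to 15, so this falls in week 3.

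**Step 2: what a patient who leaves at that point has.**

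| Measure | Schedule | Post-baseline value by session 13 |
|---|---|---|
| PSQI, section 2.7.1 | baseline, weeks 5 and 8 | none |
| PSQI, abstract | baseline, weeks 2 and 8 | week 2 only |
| Athens, SF-36 | baseline, weeks 5 and 9 | none |
| Sleep diary | daily during treatment | two full weeks and part of a third |
| ET, section 2.7.1 | baseline, weeks 3 and 5 | possibly week 3 |

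On the section 2.7.1 timetable the patient is evaluable without any post-baseline value of the primary outcome. On the abstract's timetable there is one mid-treatment score and no later one. The two timetables need reconciling in any case.

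**Step 3: possible size of the bias.** The protocol states no figure for this point, so there is none to reproduce. The inputs come from section 2.8: responders 87.5% verum and 25% sham, 20% dropout, 111 per group. Three assumptions are added: both acupoint arms respond at 87.5%, the 20% is the average over the three equal arms, and in the extreme case only non-responders leave, at the same rate in every arm.

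- Mean non-response = (12.5 + 12.5 + 75)/3 = 33.3%.
- Share of non-responders leaving = 20/33.3 = 60%.
- Loss per acupoint arm = 0.60 × 12.5 = 7.5%, about 8 of 111.
- Loss in the control arm = 0.60 × 75 = 45%, about 50 of 111.
- Observed responders, acupoint = 87.5/(100 − 7.5) = 94.6%.
- Observed responders, control = 25/(100 − 45) = 45.5%.
- Observed difference = 94.6 − 45.5 = 49.1 points, against a true 87.5 − 25 = 62.5.

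**Step 4: the range.** If dropout is unrelated to response within each arm, the expected difference stays at 62.5 points. For an intermediate case, let half of the dropout (10%) be non-responders leaving and the other half be unrelated to response:

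- Share of non-responders leaving = 10/33.3 = 30%.
- Losses tied to non-response = 0.30 × 12.5 = 3.75% and 0.30 × 75 = 22.5%.
- Observed responders = 87.5/96.25 = 90.9% and 25/77.5 = 32.3%.
- Observed difference = 58.7 points.

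The unrelated half does not change these proportions in expectation.

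**The case against.** The strongest reply is that the protocol already intends continued assessment. Item 3, the statement that all patients complete the PSQI and the statement that all are recorded to the end point that way. The third task in item 1 may, in translated text, mean completing the outstanding assessments. Item 2 is a care provision for people already out of the trial and does not itself order anyone's withdrawal. A condensed article may also leave visit instructions to the full protocol.

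Much of this stands. A reader might infer that only the reason and the last treatment date are collected, and that dropouts therefore have no PSQI. The documents do not support that: item 1 lists a third task, every patient has a baseline PSQI, and the abstract would add one at week 2. Nor is it right that an evaluable dropout leaves nothing to evaluate, since diary data exist on either timetable.

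A reader might also take the section 2.4.1 sentence as permission to stop outcome visits. It stands between tracking abnormal tests back to normal and choosing a follow-up method by the degree of the event, so it most naturally concerns adverse-event follow-up.

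The contradiction remains, because it lies in statements the article does make. The generous reading of item 1 does not close the gap either, because contact is triggered by the dropout and not by week 5 or 8. The PSQI covers one month, so one taken at a week-3 contact would reach back before randomisation and could not stand in for the scheduled value.

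**Conclusion.** The point holds as an unresolved contradiction, not as proof that the PSQI goes uncollected. No sentence says outright that the PSQI is sought after acupuncture stops. On the section 2.7.1 timetable, the half-course threshold falls before the first post-baseline PSQI.

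On the protocol's own rates, the acupoint-versus-control difference of 62.5 points could appear as anything from about 49 points to 62.5. The lower end is an extreme. The range assumes that those who leave tend to be non-responders; if patients who felt well also left, the picture would change. In this illustration the bias shrinks the difference, so it does not point to a false claim of benefit. It uses responder rates because those are the figures given, while section 2.9.1 analyses change scores, for which no size can be derived.

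A reader might extend the argument to the compatibility-versus-single comparison. The illustration gives no support for that: it assumes equal acupoint arms, so the bias there is zero by construction, and the protocol gives no separate rates.

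The change is worth making because missed values cannot be recovered and the remedy is cheap.

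**What to change.** - **Section 2.4 items 1, 2 and 4:** reconcile them with item 3 and section 2.7.1 by stating that a patient who stops acupuncture stays in the assessment schedule unless consent to data collection is withdrawn.
- **Section 2.4 item 1:** replace the unclear third task with a requirement to obtain the PSQI and Athens scale at the scheduled end-of-treatment and follow-up time points, through the contact routes already listed. Both scales are self-rated.
- **Records:** note the date and type of any other sleep treatment started after stopping.
- **Section 2.9.1:** state that these values enter the ITT analysis.
- **Section 2.4.1:** clarify only that the sentence on ending observation refers to adverse-event follow-up and does not end outcome assessment.

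The cost is protocol wording and about one CRF page. Contact with dropouts is already required, so the added burden is some extra calls and some PSQI values obtained by phone or letter.

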### Elimination and shedding standards

2.3

1.Cases that meet the exclusion criteria.2.Those who fail to comply with the prescribed treatment or have incomplete data affecting the evaluation of efficacy and safety should be excluded.3.Subjects with poor compliance who quit on their own during the course of treatment.4.Combined use of therapeutic methods that are prohibited under this programme or replacement of treatment methods on their own.5.If serious adverse events or complications occur, and it is not appropriate to continue the treatment; treatment should be discontinued.

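### Treated plan violators are dropped from the adverse-reaction evaluation, against the protocol's own rules, and the adverse-event window does not match the trial's schedule

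*Protocol article*

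**What the plan says.** **Violators.** Item 4 of section 2.4 (The treatment of removed cases) says that patients who violate the plan "will not be evaluated for efficacy or adverse reactions". Its examples are "violation of the combination of drugs, violation of the inclusion criteria, and medication compliance". Item 3 of the same section says: "When a subject is assigned a random number, he/she becomes an object of the experimental observation, regardless of future diagnosis or the integrity of the" treatment. The opening sentence of item 4 treats dropouts as a separate class. Those who completed at least half the course count for efficacy. The garbled clause on shorter courses appears to keep those patients for adverse reactions only.

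**Related rules.** Section 2.3 adds that those who do not comply or "have incomplete data affecting the evaluation of efficacy and safety should be excluded". Section 2.4.1 (headed 2.2.6 Management of Adverse Events) asks for adverse events to be documented in detail, related to treatment or not. Section 2.9.3 (Safety analysis) tabulates the number and probability of events and names no population.

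**Window.** Section 2.7.1 (Outcome measurement) has adverse events "recorded during the 4 treatment weeks and the 12 follow-up weeks". In the next paragraph, drop-outs, withdrawals and compliance are "recorded during the treatment weeks and the 4 follow-up weeks". Sections 2.1 and 2.6 give 5 weeks of treatment, 25 sessions and one follow-up in the fourth week afterwards. Section 2.1 puts the total observation period at 10 weeks, including 1 baseline week.

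**Serious events.** Section 2.4.1 requires a report "within 20 hours or no later than the second working day".

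**The concern.** A harm rate should describe everyone exposed to the treatment. Here one class of exposed patients is taken out of the safety evaluation by an express rule, for reasons that can arise, or come to light, after needling has begun. Some of those reasons may be tied to harm. A patient who takes a prohibited drug for needling pain is one example. Another is a patient who should have been excluded under section 2.2.3 for susceptibility to bleeding and who then bleeds. If violators have more events than the rest, the reported rate is too low. The arms also differ in the number of points needled (one against three, section 2.5.1), so the loss need not be equal between them.

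The window is a second and separate fault. With two incompatible statements of how long events are recorded, centers could collect over different periods, and the time at risk behind each rate is not fixed.

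**Working it through.** **1. The plan's own timeline (sections 2.1 and 2.6).**
- Baseline 1 + treatment 5 + follow-up 4 = 10 weeks. This reproduces the stated observation period.
- 25 sessions / 5 weeks = 5 sessions per week, which agrees with five consecutive days and a two-day break.
- After randomization: 5 + 4 = 9 weeks.

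**2. The adverse-event window (section 2.7.1).**
- 4 + 12 = 16 weeks, and 16 − 9 = 7 weeks beyond the last scheduled follow-up.
- Four treatment weeks hold 4 × 5 = 20 of the 25 sessions. The other 5 fall in week 5. If the 16 weeks run without a gap, week 5 lies inside the window but is labelled follow-up.
- The same section uses 4 follow-up weeks for drop-outs and compliance, so the 12 conflicts with its own section as well as with the schedule.

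**3. The violator rule, rule by rule.**

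| Place | Effect on a treated violator |
|---|---|
| 2.4 item 3 | Stays under observation |
| 2.4 item 4, violators | Out of efficacy and of adverse-reaction evaluation |
| 2.4.1 | Events recorded in detail |
| 2.9.3 | Events tabulated; no population named, so item 4 is not overridden |

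Events are therefore recorded and then dropped at evaluation. The ITT and PP sets in section 2.9.1 stand under the efficacy analysis and do not settle who is in the safety tables.

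**4. Possible size.** The article gives neither a violator share nor an event rate, so all inputs here are assumptions. Let v be the violator share, r0 = 10% the event rate in the others and r1 the rate in violators. Violators leave both numerator and denominator.
- Reported rate = r0 = 10%.
- True rate = (1 − v) × r0 + v × r1.
- Reported − true = −v × (r1 − r0).
- Share of affected patients dropped = v × r1 / true rate.

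| v | r1 | True rate | Affected patients dropped |
|---|---|---|---|
| 5% | 10% | 10.0% | 5.0% |
| 5% | 20% | 10.5% | 9.5% |
| 5% | 30% | 11.0% | 13.6% |
| 10% | 10% | 10.0% | 10.0% |
| 10% | 20% | 11.0% | 18.2% |
| 10% | 30% | 12.0% | 25.0% |
| 20% | 10% | 10.0% | 20.0% |
| 20% | 20% | 12.0% | 33.3% |
| 20% | 30% | 14.0% | 42.9% |

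Last row: 0.80 × 10% + 0.20 × 30% = 14%, and 0.20 × 30% / 14% = 42.9%. With equal rates (r1 = r0) the reported rate is unbiased, but the violators' events are still missing from the tables.

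**The case against.** **Collection is protected.** Sections 2.4 (item 3), 2.4.1 and 2.7.1 keep patients under observation and have events recorded, and section 2.9.3 repeats no exclusion. This stands as far as collection goes, and it rules out saying that safety data are certain to be lost. It does not cancel an express instruction not to evaluate.

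**The analysis plan is not shown.** A full plan may define a safety set. That would be a fair reply to an omission. Here the article states a rule, and a safety set of all treated patients would contradict it.

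**Those who stop because of harm are not the violators.** A reader might infer that patients who quit because of pain, fainting or bleeding are the likeliest to be dropped. The text does not support this. Dropouts have their own rule in item 4, which appears to keep early ones for adverse reactions. The link to harm is plausible for prohibited co-treatment, non-compliance and some eligibility breaches, but the article gives no data on it.

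**The window loses nothing for certain.** It is tempting to read it as leaving out week 5, and with it 5 of 25 sessions (20% of exposure). A continuous 16 weeks contains week 5, so no such loss is shown. The overrun counted from randomization is 7 weeks. A figure of 8 needs the 12 follow-up weeks to start after week 5 (12 − 4). The window as written is also common to all three arms, so it does not by itself bias the comparison between them.

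**Safety is descriptive.** A chi-square test is used only if necessary, and the PSQI comparison is untouched. That is true and limits the consequence to the harm results.

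**Conclusion.** The concern holds in two parts of unequal weight.

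The violator rule in section 2.4 is wrong as written. It contradicts item 3 of its own section, sits against section 2.4.1, and is not undone by section 2.9.3. Reported rates can be biased by an unknown amount. Over the assumed range, a reported 10% corresponds to a true 10% to 14%, so the understatement runs from nothing to 4 percentage points, and 5% to 43% of affected patients leave the tables. No single value in that range can be claimed. If violators had fewer events than the others, the bias would go the other way.

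The window in section 2.7.1 is an internal contradiction: 16 weeks against 9 after randomization. It makes the exposure period ambiguous and does not prove that any event is missed.

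The serious-event limit in section 2.4.1 names two deadlines that need not coincide. It has no bearing on event rates and is a minor separate point.

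**What to change.** 1. In section 2.4, item 4, strike the reference to adverse reactions so that the violator exclusion applies to efficacy only. State in section 2.9.3 that safety is tabulated in all patients who received at least one session, whatever their later compliance, eligibility finding or co-treatment. Say in section 2.3 that its exclusions do not remove anyone from that set.
2. Reconcile the adverse-event window in section 2.7.1 with sections 2.1 and 2.6, and state one window that covers all 5 treatment weeks and the trial's follow-up. Use the same follow-up length for events, drop-outs and compliance.
3. Reconcile the two serious-event reporting limits in section 2.4.1 into one statement.

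The cost is protocol and case report form wording. No added visits or patients are needed, because section 2.4.1 already asks for the events to be recorded.
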